## Interim Analyses

Once 50% of patients have been recruited or 1 year has passed, whichever is sooner, the study statistician will perform a blinded descriptive analysis of participants’ baseline characteristics and safety data, which will be reviewed by the Data Safety Monitoring Board (DSMB).

## 8.4 Role of the Data Safety Monitoring Board

This study will be monitored by an independent Data Safety Monitoring Board (DSMB), consisting of an independent physician, and two other members not involved in this study. The DSMB will be immediately informed of any serious adverse events (SAEs), both related and unrelated,. If at any point the DSMB considers continuance of the study unacceptable the steering committee will be immediately notified.

Interim reports, prepared by the data management team for the study, for review by the DSMB will include data on recruitment, compliance, adverse effects, baseline comparability and treatment comparisons. An agreed upon review package which contains the appropriate data summary by treatment will be provided by the study statistician for the purposes of these reviews. DSMB members will review data only by masked study group (such as A vs. B rather than experimental vs. control). The DSMB may request unblinded safety data tables, in case of adverse events associated with study drug or procedures.

Serious adverse events, which are of concern to members of the Steering Committee (potentially study drug related) will also be reviewed by the DSMB.

Members of the DSMB will also be responsible for developing terms of reference including clinical stopping rules. If at any point the DSMB considers continuance of the study unacceptable, the steering committee will be immediately notified.

# Safety and Adverse Events

The study Investigators will comply with ICH Guidelines, as per GCP section 4.11, Health Canada Regulations, and their local REB requirements to submit any new adverse events that are both serious and unexpected. Any new information regarding the safety of research subjects should also be submitted.

## 9.1 Definitions

Serious Adverse Event (SAE)

Adverse events are classified as serious or non-serious. A serious adverse event is any AE that is:

- fatal
- life-threatening
- requires or prolongs hospital stay
- results in persistent or significant disability or incapacity
- a congenital anomaly or birth defect
- an important medical event

Important medical events are those that may not be immediately life threatening, but are clearly of major clinical significance. They may jeopardize the subject, and may require intervention to prevent one of the other serious outcomes noted above.

## 9.2 Reporting of Serious Adverse Events

For this study only Serious Adverse Events will be reported.

A related serious adverse event must be reported to the sponsor, the local REB and the applicable Regulatory body (Health Canada) as soon as possible but no later than 7 calendar days after first knowledge of the event. Further information and significant new information on ongoing serious adverse events will be provided to the sponsor, the REB and Health Canada. Copies of all information about the SAE will be kept in the Regulatory binder.

All SAEs will be followed until resolution or until the Principal investigator is of the opinion that the SAE has stabilized and no more follow-up is required. SAEs will be reported using the REDCap EDC system. The SAE must be entered into the REDCap SAE reporting page within 24 hours of learning of the event. Once the information is entered an email will be automatically sent to the Principal Investigator informing her of the event.

**Morbidities or Complications of prematurity**

- Air leaks (pneumothorax, pneumomediastinum, pneumopericardium, pneumoperitoneum)
- Necrotizing enterocolitis (NEC) of stage 2 or greater as per modified Bell’s criteria (16)
- Patent ductus arteriosus (PDA) documented by echocardiography, medically treated / surgically ligated / haemodinamically significant
- Pulmonary interstitial emphysema
- Pulmonary hemorrhage
- Intraventricular hemorrhage according to Papile’s classification (17)
- Periventricular leukomalacia (PVL) identified by cranial ultrasound(18)
- Retinopathy of prematurity (ROP) (19)
- Bacterial sepsis and/or meningitis
- Bronchopulmonary dysplasia (BPD) (20)

Presence of the following abnormal laboratory values:

- hypoglycemia
- hyperglycemia
- hypocalcemia
- hypercalcemia
- hyponatremia
- hypernatremia

The complications of prematurity, listed above, are clinically expected outcomes in preterm neonates aged between 24 and 32 weeks, therefore not subject to expedited reporting.

However, a worsening of these clinical outcomes that occurs after study drug administration will be recorded as ADRs if related to study drug and subject to expedited reporting if serious.

The complications of prematurity will be recorded in the electronic case report form (eCRF) as clinical documentation of each neonate. Specifically the details are as follows:

- Presence / Absence
- Start date and start time
- Ongoing / Solved
- If solved, End date and end time
- In case of sepsis, also number of occurrences

## 9.4 Treatment Discontinuation

The criteria for permanent discontinuation of further study product/interventions for an individual subject are as follows:

- Completion of treatment/intervention as defined by the protocol
- Clinical reasons believed to be life-threatening by the physician
- SAE occurring during and shortly after administration of the study drug

The infant will continue to be followed with the parent’s/LAR’s permission if the study treatment/intervention is discontinued. There will be no changes to the follow-up time point schedule, except no study treatment/intervention will be administered.

## 9.5 Premature Study Discontinuation for an Individual Subject

The criteria for permanent discontinuation from the study for an individual subject are as follows:

- Request of the infant’s parent/LAR to withdraw from the trial
- Any clinical adverse event, laboratory abnormality, intercurrent illness, other medical condition or situation occurs such that continued participation in the study would not be in the best interest of the infant.

In the event that the infant is withdrawn from the study due to an SAE, this will be recorded in the eCRF and in the source documentation. The infant will be followed and treated by the Investigator until the abnormal parameter or symptom has resolved or stabilized. It will be up to the clinician to determine that the SAE is either resolved or that it has reached a stable state, after which no further follow-up is necessary. There will be source documentation to support this determination.

## 9.6 Protocol Violations/Deviations

Protocol violations/deviations will be reported by all study sites. Each site will keep a log of protocol violations/deviations that will be compiled at the end of the study. Each site will be responsible to report violations and deviations to their respective REBs, as per local requirements.

If any subject receives the incorrect study drug, this information will be reported to the sponsor.

If an infant requires more than one dose of study medication and it is discovered that the incorrect drug has been dispensed then this will be reported. The infant will be removed from the study but will be followed until the last timepoint of the study for safety reasons.

# Data Handling and Record Keeping

## Data Management Responsibilities

Data collection will be the responsibility of the research staff at each site under the supervision of the Principal Investigator and Sub-Investigators. During the study the investigator will maintain complete and accurate documentation for the study.

Data collection for the study will be done using an eCRF (REDCap). Both study centers will enter study information into this system. All information will be de-identified, using a unique subject number for each infant enrolled into the study.

All source documents and lab reports must be reviewed by the clinical team and data entry staff, who will ensure that they are accurate and complete. Adverse events will be graded, assessed by severity and causality and reviewed by the site investigator or designee.

## Confidentiality

All subject related information including Case Report Forms, evaluation forms, reports, etc. will be kept strictly confidential. All records will be kept in a secure, locked location and only research staff will have access to the records. Subjects will be identified only by means of a coded number specific to each subject. All computerized databases will identify subjects by numeric codes only, and will be password protected or encrypted.

Upon request, subject records will be made available to the study sponsor, monitoring groups’ representative of the study sponsor, and applicable regulatory agencies such as Health Canada.

## Record Retention

All research records for this trial (as it falls under Health Canada Division 5 regulations) will be retained for a minimum of 25 years after study closure.

# Quality Control and Quality Assurance

The trial will be conducted in accordance with the latest version of the Declaration of Helsinki, GCP, ICH regulatory guidelines, and Division 5 of Health Canada Food and Drug regulations and requirements regarding ethical committee review, informed consent, and other statutes and regulations regarding the protection of the rights and welfare participants participating in the study.

The protocol, including the informed consent document and all recruiting materials, will be submitted to the Research Ethics Boards for review and approval. No changes will be made to the protocol without REB approval, except where necessary to eliminate apparent immediate hazards to participants. The parent/LAR will be able to withdraw their consent to participate at any time without prejudice. Additionally, the investigators may withdraw an infant if, in the investigator’s clinical judgment, it is in the best interest of the infant.

Data will be collected using REDCap EDC. This system will be used to generate reports. There is also an audit trail function which is compliant with current Canadian regulations.

Source documents (version controlled) will be provided by the sponsor. These documents will be monitored by a representative of the sponsor.

## Study Monitoring Plan

On-site monitoring will be conducted by qualified research personnel. The Monitoring time points will occur approximately every 6-12 months or as needed, based on enrollment and subject study time points. The Essential Documents in the Investigator Regulatory Files will be monitored using the Monitoring Timepoint Report template. The monitor will identify any items missing from the Regulatory Binder. Site personnel are responsible for maintenance of the Regulatory Binder. The consent document will be reviewed for content to ensure it contains the required (and additional, as applicable) regulatory elements. The consent document will be compared to the protocol and site specific REB procedures for informed consent documentation to ensure agreement between the two documents. Consent form monitoring will be documented in the monitoring time point report.

## Ethical Considerations

This study will be conducted according to Canadian and international standards of Good Clinical Practice for all studies. Applicable government regulations and local study center research policies and procedures will also be followed.

This protocol and any amendments will be submitted to local REB for formal approval to conduct the study. The decision of the REB concerning the conduct of the study will be made in writing to the investigator.

All parents of infants for this study will be provided a consent form, describing the study and providing sufficient information for them to make an informed decision about their infant’s participation in the study. The consent form will be submitted with the protocol for review and approval by the REB. The formal consent of a subject, using the REB-approved consent form, will be obtained before the infant is submitted to any study procedure. This consent form must be signed by the infant’s parent or legally acceptable representative, and the investigator-designated research professional obtaining the consent.

# Budget & Finance

This trial is funded by the AHSC (Academic Health Science Centers) AFP (Alternate Funding Plan) Innovation Fund. The study drug (Curosurf®) will be provided in-kind by Chiesi Pharmaceuticals S.p.A.

# Publication Plan

Results of the study will be presented at relevant national and international scientific meetings and submitted for publication in a relevant peer-reviewed journal. Approval from the primary responsible party ([name]) must be obtained before any information can be used or passed on to a third party.

| Con Meds | X |  |  |  |  |  | X | X | X | X | X |
| SAE assessment |  | X | X | X | X | X | X | X | X | X | X |
| Extubation failure assessment |  |  |  |  |  |  |  | X | X | X | X |
| Secondary outcome assessment |  |  |  |  |  |  |  |  |  |  | X |

# Appendices

# Appendix A: Time table of Events

1 Consent may be obtained from the mother antenatally or after the birth of the infant.

2 Includes weight, Temperature (Axillary), heart rate (apical), respirations.

3 Includes Rate, PIP, PEEP, FiO2, Mean, IT, and Tidal volume

***** Data collection at this time point is not done if the infant has already been discharged.

# Appendix B: Extubation Criteria

Infants enrolled in the study will be extubated when they meet all of the following criteria:

1. rate on ventilator ≤40 per minute and
2. mean airway pressure ≤ 10 cm H20 and
3. fi02 ≤ 30%

Individual physicians can extubate patients from higher settings, at their discretion.

# Appendix C: Extubation Failure Criteria

The following are the criteria used to decide to reintubate a baby <30 weeks gestational age after a period of extubation on non-invasive respiratory support or low flow oxygen. Small variances of these parameters are allowed within the protocol (indicated in brackets),

RDS score (validated respiratory distress score) > 8 OR >1 of the following:

1) FiO2 ≥ 40% (±2%) & climbing;

2) pH<7.20(±0.1) and pCO2>60 (±2 ), (persistent & associated with clinical distress) or

3) recurrent apnea (6/6h requiring stimulation or >2 on 2 consecutive hours or 1 requiring bagging).

A baby will be considered as having failed extubation if he/she requires reintubation within 72 hours of extubation.

# Appendix D: Secondary Outcomes

1. Extubation failure (defined as in Appendix C )

2. Duration of first intubation (in hours/days)

3. Total duration of respiratory support (ventilator and nCPAP) and

Total number of days of oxygen requirement

4. Number of doses of surfactant received

5. Adverse events during or after administration of surfactant:

a) Severe airway obstruction, defined as sudden and severe desaturation < 80% with bradycardia (heart rate <100 bpm) with absence of visualization of chest movements with no response to increases in ventilator pressure or bagging for ≥3 minutes and requiring suctioning of surfactant or change of endotracheal tube (ETT)

b) Need for cardiopulmonary resuscitation

c) Pulmonary hemorrhage, defined as fresh blood in the ETT lumen associated with an increase in ventilation or oxygen requirements

d) Pulmonary air leaks (pneumothorax and/or pulmonary interstitial emphysema (PIE) on CXR)

6. Bronchopulmonary dysplasia, defined as oxygen or respiratory support requirement at 36 weeks corrected GA

7. Mortality prior to discharge

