# Study Objectives

The objective of the study is to compare the efficacy of the 2 surfactants Curosurf® and BLES®, at facilitating extubation and reducing pulmonary morbidities and also to compare the adverse events during surfactant administration in very premature infants. We hypothesize that, compared to BLES®, Curosurf® will increase the proportion of infants alive and extubated within 48 hours after surfactant therapy.

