## Study Endpoints

**Primary Endpoint**

The primary efficacy endpoint is that the patient is alive and extubated at 48 hours post surfactant administration. We hypothesize that Curosurf® will increase the proportion of infants alive and extubated within 48 hours after surfactant therapy.

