# Study Medication/Intervention

Infants will be randomized in a 1:1 manner, to receive either the study drug, Curosurf® or the control drug, BLES®. The treatment dose for Curosurf® is 2.5 ml/kg (200mg/kg) for the first dose and 1.25 ml/kg (100mg/kg) for repeat doses. For BLES® the recommended dose is 5 ml/kg. Either drug is given by syringe into the endotracheal tube by a Respiratory Therapist. The SOP for administering both study drugs is found in Appendix E of this protocol.

After consent is obtained, and all inclusion/exclusion criteria are fulfilled an infant can be randomized into the trial. A blinded study RT will administer the drug according to the SOP found in Appendix E (also in the Resource Manual). The RT will document the procedure using the source documents provided by the sponsor and will also complete all Drug Accountability logs, as appropriate. Detailed instructions for completion of drug accountability logs are found in the Resource Manual.

The blinding procedure for administration of both study drugs is as follows:

- As the volume and viscosity of Curosurf® and BLES® are different, blinding of the RT administering the surfactant is not feasible. However, at any given time, two RTs work in the NICU. Doses of surfactant will be prepared away from the bedside by a RT not otherwise involved in the care of the infant. The surfactant will be drawn into a syringe and placed in a covered box. The RT will administer the surfactant with the syringe masked by a large label covering the amount of the contents. The RT will record in the patient’s chart that surfactant was provided but will not include the name or the dose of the product. This RT will not care directly for the infant for at least 48 hours following administration of the surfactant. The clinical and research teams will be blinded to the identity of the assigned surfactant throughout the study, unless an emergency occurs requiring unblinding

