# Statistical Plan

## 8.1 Sample Size Determination

Review of our data on duration of ventilation indicates that in 2010, 40% of patients meeting inclusion criteria were alive and extubated 48 hours after BLES®. We anticipate that the mean length of ventilation in the BLES® group will be similar or shorter in 2012. We therefore based our sample size calculation on the percentage of successful extubation within 48 hours in the BLES® group lying between 40% and 55%. Fixing the probability of type-I error at 5%, a sample of size of 44 per group will provide power in excess of 80% to detect an absolute difference of 30% in the percentage still intubated at 48 hours. (See Table)

| Percentage alive and extubated at 48 hrs | |  |  |
| --- | --- | --- | --- |
| BLES® group | **Detectable in Curosurf® group** | Risk difference | Relative risk reduction |
| 40% | **69.3%** | 29.3% | 0.488 |
| 45% | **73.9%** | 28.9% | 0.525 |
| 50% | **78.3%** | 28.3% | 0.566 |
| 55% | **82.3%** | 27.3% | 0.607 |

A recent RCT in a similar population found that 52% of infants who received Curosurf® were extubated by 48h compared to 22% of infants who received Survanta, an absolute reduction of 30% (15).

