## 8.2 Statistical Methods

Demographic and clinical characteristics of patients at baseline will be summarized by treatment group. Continuous variables will be summarized using mean, standard deviation, median, and interquartile range, as appropriate. Discrete variables will be summarized using frequency and percent. Analysis of the primary outcome will use logistic regression, with treatment group as the main independent variable, and adjusting for the stratification variables, centre and gestational age category. The intention to treat principle will be followed. Secondary analyses will include comparison of mortality rates by treatment group using a similar logistic regression model. Use of oxygen at 36 weeks will be analyzed similarly. Cox regression will be used to compare duration of ventilation by treatment group, adjusting for centre and gestational age category. Duration of oxygen support will be analyzed similarly. Durations for any patients who die while still on ventilation will be treated as censored values. Incidence of adverse events by treatment group will be summarized descriptively.

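### Secondary outcome 5c counts pulmonary hemorrhage only when blood is seen in the endotracheal tube, so its incidence can tend to favour the arm extubated sooner

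*Protocol*

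**What the plan says.** Protocol Appendix D, item 5, lists "Adverse events during or after administration of surfactant" as a secondary outcome and gives no end to the period. Component 5c is "Pulmonary hemorrhage, defined as fresh blood in the ETT lumen associated with an increase in ventilation or oxygen requirements". It has no alternative criterion for an infant without a tube.

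Protocol section 8.2 states: "Incidence of adverse events by treatment group will be summarized descriptively". No time-at-risk denominator is mentioned.

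The Study Objectives hypothesise that "Curosurf® will increase the proportion of infants alive and extubated within 48 hours after surfactant therapy". The first row of the table in section 8.1 is "40% | 69.3% | 29.3% | 0.488", that is, 40% alive and extubated at 48 hours with BLES against 69.3% with Curosurf.

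Section 9.2, under the complications of prematurity, also lists pulmonary hemorrhage. There it has no definition and no reference to a tube. It is recorded in the eCRF for each neonate as present or absent, with start and end dates and times.

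**The concern.** The event cannot be counted unless a tube is in place when the blood appears or is put in afterwards. Take two infants with the same fresh airway blood and the same rise in oxygen need. The one still intubated is a case, and the one already extubated and managed without a tube is not. The treatment is expected to change how long infants stay intubated, so the chance of being counted depends on arm even if the bleeding risk does not.

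The Potential Risks section names pulmonary hemorrhage as a risk associated with surfactant, and comparing adverse events is a stated objective. At stake is a safety line that may look somewhat better for Curosurf for a reason unrelated to bleeding. A lower count could also be partly real if less intubation means less bleeding, and 5c cannot separate the two explanations.

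**Working it through.** **Plan's own figure.** Section 8.1 says "Fixing the probability of type-I error at 5%, a sample of size of 44 per group will provide power in excess of 80" per cent. A two-sided 5% test of two proportions with pooled variance, no continuity correction and 44 per group gives power of 0.799, 0.799, 0.801 and 0.799 for the four table rows. The extubation rates are therefore usable as the plan's own expectation. Two-sidedness is assumed, as the section does not state it.

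**Inputs from the protocol.** Alive and extubated at 48 h: 40% against 69.3% (first row) and 55% against 82.3% (last row). Infants per arm: 44.

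**Assumptions.**
- Extubation times are exponential. Infants who die are treated as still intubated, and later reintubation enters only through *s* below.
- The bleeding hazard is constant and equal in both arms, before and after extubation.
- The window is 72 h. In the protocol 72 h is the limit for study doses and the period for extubation failure. It is not an outcome window for 5c.
- The true risk is 5% to 10%. The protocol gives no rate.

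**Step 1, extubation hazards.** h = −ln(1 − p)/48.
- BLES, 40%: 0.5108/48 = 0.01064 per hour.
- Curosurf, 69.3%: 1.1809/48 = 0.02460 per hour.

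**Step 2, share of 72 h spent intubated.** f = (1 − exp(−72h))/(72h).
- BLES: (1 − 0.4648)/0.7662 = 0.699, or 50.3 h.
- Curosurf: (1 − 0.1701)/1.7714 = 0.469, or 33.7 h.
- For 55% against 82.3% the shares are 0.583 and 0.356.

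**Step 3, apparent risk ratio under equal true risk.** Let *s* be the share of post-extubation bleeds that are still seen in a tube after reintubation. With *a* the BLES share and *b* the Curosurf share, RR = (b + s(1 − b))/(a + s(1 − a)).

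| s | 40% vs 69.3% | 55% vs 82.3% |
|---|---|---|
| 0 | 0.67 | 0.61 |
| 0.25 | 0.78 | 0.75 |
| 0.50 | 0.86 | 0.86 |
| 0.75 | 0.94 | 0.94 |
| 1 | 1.00 | 1.00 |

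Setting RR = 0.9 gives s = (0.9a − b)/((1 − b) − 0.9(1 − a)), which is 0.62 for the first row and 0.63 for the last. The distortion therefore exceeds 10% until about 62% to 63% of post-extubation bleeds are seen.

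**Step 4, absolute size with s = 0, first row.** Expected cases = 44 × risk × f.
- 10% risk: 44 × 0.10 × 0.699 = 3.1 against 44 × 0.10 × 0.469 = 2.1, a gap of 1.0 infant.
- 5% risk: 1.5 against 1.0, a gap of 0.5 infant.
- Any *s* above 0 multiplies the gap by (1 − s).

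**Step 5, dependence on timing.** If all bleeds fall in an assumed first 24 h, f is (1 − exp(−24h))/(24h) = 0.883 against 0.755. The RR with s = 0 is then 0.755/0.883 = 0.86. Over 48 h the shares are 0.783 and 0.587, with RR 0.75. Early clustering of bleeds shrinks the distortion.

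**The case against.** Four points on the other side carry weight.

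1. **There is a second recording route.** The section 9.2 list has no tube condition and records start times, so an extubated infant who bleeds could be captured there. This largely stands. A reader might infer from 5c that a real excess of hemorrhage with Curosurf would be hidden from the trial. The documents do not support that. They show two recording routes without a shared definition, and do not say whether the 5c wording governs the section 9.2 item.

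2. **The size rests on assumptions.** The 72-hour window is not an outcome window, and the hazard may not be constant. Item 5 centres on administration, when every infant has a tube, and bleeds may cluster soon after dosing. The criteria in Appendix B select more stable infants for extubation, who may bleed less. Both would reduce the distortion. This stands and is why only ranges are given.

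3. **Reintubation may reveal the bleed.** Partly right. A substantial bleed may lead to reintubation and then meet 5c. However, Appendix C as written does not name airway blood. It needs a distress score above 8 or more than one of three other findings, whereas 5c needs only some rise in ventilation or oxygen requirement alongside the blood. Reintubation therefore cannot be relied on to close the gap, and the share it closes is unknown.

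4. **Denominators may be left to the SAP.** A per-infant summary is the natural reading of section 8.2, not its literal wording. But time-at-risk denominators would not recover bleeds that the definition excludes, and that definition is fixed in the protocol.

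**Conclusion.** The point holds as a defect of definition, of minor to moderate weight. Item 5c makes ascertainment of a named surfactant risk depend on a state that the treatment is expected to change. Under equal true risk the incidence by group can tend to favour Curosurf, provided that Curosurf does extubate sooner. With a constant hazard over 72 hours the apparent risk ratio lies between 0.61 and 0.67 if no post-extubation bleed is seen, is 0.94 if 75% are seen, and is 1.00 if all are. In 44 infants per arm at an assumed 5% to 10% risk, this is a gap of about one infant or fewer.

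A reader might go further and take this as a bias in the trial's main result. It is not: the outcome is secondary and summarised descriptively, and neither the primary test nor any stopping rule set out in the protocol depends on it. The practical harm is that, in a table with two or three cases per arm, a difference of one could be read as a safety advantage when it may reflect only who still had a tube.

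**What to change.** - Reword item 5c so that it can be met with or without a tube, for example: fresh blood from the airway, without a local source, together with an increase in respiratory support or oxygen requirement.
- Apply the same definition to the pulmonary hemorrhage item in the section 9.2 eCRF list, and record whether the infant was intubated at onset.
- Report the tube-only count alongside the broader one.
- Compare arms over a common window from first dose, stated in advance, using the start dates and times that section 9.2 already collects.

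The cost is wording in Appendix D and section 9.2, plus one eCRF field. No procedure or treatment rule changes. The downside is somewhat lower specificity in extubated infants. Since more of them are expected in the Curosurf arm, that loss may itself differ by arm and could work against Curosurf, so both counts should be shown.
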